#### Surgical technique

Excision and grafting are carried out in accordance with the local protocol of the operating burn centre. Burns will be tangentially excised using guarded knives and/or hydrosurgery. Autografts are harvested with an electrical dermatome from a preoperatively selected donor site. Autografts will be predominantly meshed. Postoperative care is equal for both treatment groups.

### Procedures

#### Conservative treatment with delayed excision and grafting if needed

Initial conservative treatment is one of the strategies used in daily clinical practice to treat deep partial-thickness burns. Patients receive conservative treatment involving the application of dressings and antimicrobial agents. These include silver sulfadiazine (Flammazine®), cerium nitrate-silver sulfadiazine (Flammacerium®), enzymatic hydrated alginate polymers (Flaminal®), or other agents and dressings according to the local protocol of the burn centre. If wound healing is not achieved after 14 to 21 days, excision and grafting of the residual defects can be performed. This is decided based on the expert opinion of the burn specialist and in consultation with the patient.

#### Early excision and grafting

Patients initially receive abovementioned topical treatment, followed by excision and grafting of the burn in the first week to ten days post-burn.

### Primary outcome

#### Scar quality

The primary outcome measure of the study is long-term scar quality assessed with the POSAS (generic version, 3.0) 12 months after discharge. The POSAS is a widely used scar quality measurement instrument that comprises two separate scales: the Patient Scale and the Observer Scale [30]. The Patient Scale includes 17 questions about visual, tactile and sensory characteristics, and the overall opinion. The Observer Scale includes eight questions assessing the scar’s pigmentation, vascularity, surface level, surface texture, firmness, adherence, tension, and overall opinion. Each item is rated on a five-point scale. The lowest score is ‘1’, which corresponds to the situation of normal skin (i.e. normal pigmentation, no itching). Score ‘5’ equals the largest difference from normal skin (i.e. the worst imaginable scar or sensation) [30].

The Patient Scale is assessed by the patient, and two independent observers assess the Observer Scale on the study area(s). The assessment is mostly done during the standard 12-month outpatient appointment by the attending burn physician(s) and/or by members of the research team. If there is no standard 12-month outpatient appointment planned, the patient is invited to attend the clinic for the scar quality assessment, for which travel and parking expenses are reimbursed. All members of the research team and the burn physicians are trained to assess scar quality with the POSAS. Each burn centre’s highly experienced head of research provides a POSAS training on the latest version: POSAS 3.0 [30].

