## Materials and methods

### Study design

A multicentre prospective study with a 12-month follow-up period will be conducted in the three Dutch burn centres: Maasstad Hospital Rotterdam, Red Cross Hospital Beverwijk, and Martini Hospital Groningen. Patients with deep partial-thickness burns, scanned as yellow by Laser Doppler Imaging (LDI), will be monitored during 18 months; two nine-month periods with either therapy as the treatment of choice in one of the periods. This time period was chosen based on expected numbers and project logistics, such as staffing. Standard care in the Netherlands for deep partial-thickness burns is predominantly conservative treatment with delayed excision and grafting if needed. However, early excision and grafting is applied if deemed more appropriate for a specific patient. The first nine-month period (July 15^th^ 2022 to April 14^th^ 2023) this strategy is followed. In the following nine-month period (April 15^th^ 2023 to January 14^th^ 2024) clinical practice will be changed: early excision and grafting will be the primary treatment. However, in specific cases e.g. based on clinical expertise, conservative treatment can be applied. Depending on the received treatment, patients will be categorized as either the conservative treatment group with delayed excision and grafting if needed, or the early excision and grafting group.

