### Participants

#### Selection

Neither, randomisation nor blinding will take place. The used treatment strategy determines to which group the patient is assigned. The first group represents conservative treatment with delayed excision and grafting if needed, the second group represents early excision and grafting. If a patient is eligible for the study, a member of the research team will provide information about the study. The patient is asked for consent to take additional measurements 12 months after discharge. After reflection time and written informed consent, the patient is included.

Anyone using the protocol must consider the ethical implications of the timing of surgery in their own practice setting. To ensure patient safety, the attending physician is justified in deciding not to start or discontinue treatment from the allocated treatment, based on sound medical grounds and after consulting with the health care team. Deviation from the assigned treatment should be rare, and the reason must be thoroughly documented.

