#### Burn wound area selection

Based on the healing potential, the attending physician will determine whether the patient has burns that meet the inclusion criteria. A maximum of two inclusion criteria-meeting burns per patient are followed for the study.

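### Attending burn physicians may fill both observer places on the primary outcome's Observer Scale, and nothing excludes those who took part in that patient's treatment decision

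*Protocol article*

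**What the plan says.** Under Scar quality, the protocol article gives the POSAS two separate scales. The Patient Scale has 17 questions and the Observer Scale has eight, one of them an overall opinion; every item is scored from 1 to 5. Two observers, described as independent, score the Observer Scale. The article does not say what they are independent of. The next sentence says the assessment is mostly done at the standard 12-month outpatient visit, "by the attending burn physician(s) and/or by members of the research team". The section adds that "All members of the research team and the burn physicians are trained to assess scar quality with the POSAS".

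Other sections describe what these physicians do earlier:

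- Selection: "Neither, randomisation nor blinding will take place". It also says that, on medical grounds and after consultation, "the attending physician is justified in deciding not to start or discontinue treatment from the allocated treatment".
- Burn wound area selection: "the attending physician will determine whether the patient has burns that meet the inclusion criteria".
- Conservative treatment with delayed excision and grafting if needed, on later surgery for residual defects: "This is decided based on the expert opinion of the burn specialist and in consultation with the patient".
- Study design: "Depending on the received treatment, patients will be categorized as either the conservative treatment group" or the early excision and grafting group.

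**The concern.** The article does more than stay silent on who rates. It names the eligible raters, and the plural with and/or lets attending physicians take both places. No sentence keeps out a physician who helped decide that patient's treatment. Because the group follows the treatment received, such a physician could help determine a patient's group and then score the result that counts for that group.

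The observer items are graded judgements, so they are open to expectation. Two observers reduce random rating error, but a view held by the whole treating team stays in the average. The adjustment described under Statistical analysis covers patient, burn and burn centre characteristics, not who rated. A shift of this kind would look the same as a treatment effect on the Observer Scale.

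**Working it through.** **Reading the sections together.**

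1. Who may rate: attending burn physicians, research-team members, or a mix (Scar quality).
2. What attending physicians do earlier: they judge whether burns qualify (Burn wound area selection) and may depart from the allocated treatment (Selection). The burn specialist decides on delayed surgery (Conservative treatment).
3. What defines the group: treatment received (Study design).
4. What separates 1 from 2: no blinding (Selection), and independence is left undefined. It may mean only that the two observers score separately.
5. Share of the instrument: 8 / (17 + 8) = 8/25 = 32% of the items.
6. Whether other raters exist: all research-team members are POSAS-trained and already named as assessors (Scar quality), and the Discussion cites the availability of trained staff when explaining why standardized images were not chosen.

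**Illustration of size.** There is no figure of the plan's own to reproduce. The Sample size section reports no formal calculation and gives only an expected maximum of 204 patients.

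Assumptions: all 204 patients are analysed, split 102/102 or (for contrast) 136/68; two-sided alpha is 0.05, a level the article does not state; there is no true difference and no confounding; raters move the between-group difference by b, in SD units of the analysed observer score. Only a shift that differs between groups matters, because one common to both cancels.

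- SE = sqrt(1/n1 + 1/n2). For 102/102 this is sqrt(2/102) = 0.140. For 136/68 it is sqrt(1/136 + 1/68) = 0.149.
- P(significant) = Φ(b/SE − 1.96) + Φ(−b/SE − 1.96).
- Example, b = 0.2 with 102/102: b/SE = 1.428, so Φ(−0.532) + Φ(−3.388) = 0.298.

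If both observers carry the same shift b, their average carries (b + b)/2 = b. If only one carries it, the average carries (b + 0)/2 = b/2. The half-shift columns show that case.

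| Assumed b (SD) | 102/102, full | 102/102, half | 136/68, full | 136/68, half |
|---|---|---|---|---|
| 0 | 5.0% | 5.0% | 5.0% | 5.0% |
| 0.1 | 11.0% | 6.5% | 10.3% | 6.3% |
| 0.2 | 29.8% | 11.0% | 27.0% | 10.3% |
| 0.3 | 57.2% | 18.8% | 52.4% | 17.3% |

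More patients would not help: SE falls while b stays, so the false-positive rate rises.

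**The case against.** The strongest reply is that the link between rater and treatment is inferred. A reader might conclude that the observers are the physicians who chose and performed the patient's treatment. The article does not say so. Surgical technique does not name who operates, the delayed-surgery decision belongs to the burn specialist, and the attending physician at a 12-month visit need not be the one who treated the patient a year before. This stands: the text permits the overlap but does not report it.

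A reader might also infer that any bias favours the newly introduced early surgery. That is unsupported. Study design describes Dutch standard care as mainly conservative, so clinicians might equally favour what they know. Nor does anything show that the mix of rater types differs between the two periods.

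It can further be said that masking would largely fail. The periods are consecutive calendar blocks, so apart from some overlap due to length of stay the visit date reveals the period. Grafts are mostly meshed and may be recognisable. Research-team raters are unblinded too and are not neutral merely by role. All of this stands and makes the remedy partial. It does not justify allowing both places to go to people involved in the treatment decision, because having made that decision is a source of expectation separate from recognising a graft.

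Two replies carry less weight. Disclosing that there is no blinding does not explain the choice of raters. Usual-care treatment does not require treating-team scoring either: the 12-month POSAS is an added measurement with its own consent and ethics request. A journal article may leave rater logistics to a fuller document, but this one states the rule, and the rule as stated is too wide.

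**Conclusion.** The point holds as an avoidable route for bias, not as a demonstrated bias. The rater rule lets attending physicians, possibly including those involved in that patient's treatment decision, make both ratings on the Observer Scale. With no blinding and groups formed by treatment received, expectation bias can enter that comparison.

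The size is not known. The percentages under the working rest wholly on assumed shifts, the maximum sample and an assumed alpha, and would apply to any unblinded two-group comparison of this size. The 5% baseline also assumes no confounding, which a non-randomised study cannot take for granted.

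The reach is limited. It would be too strong to call the Observer Scale half of the primary outcome: it is one of two separate scales and 8 of 25 items, and the article states no combined score. The Patient Scale is scored by unblinded patients and lies outside this point. A change is worth making because a narrower rule can draw on raters the article already names and trains.

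**What to change.** In Scar quality, make these changes:

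1. Require that at least one of the two observers, and both where staffing allows, is a POSAS-trained research-team member or burn physician who did not choose or perform that patient's treatment. This also gives the word independent a stated meaning.
2. Do not give raters the operation record before they score.
3. Record each rater's role for every assessment. The first 12-month POSAS took place on 30 June 2023 and collection was expected to run to January 2025 (Study status and timeline), so recover the role retrospectively for visits already done where possible.
4. Repeat the Observer Scale analysis using ratings from uninvolved raters only, and report it beside the main result.

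No additional assessor is needed in principle, because two observers and a trained pool are already planned. The cost is some rescheduling at the 12-month visit. The article gives no staffing numbers per centre, which is why the minimum is one uninvolved rater. The remedy is partial: visit date and meshed grafts may still reveal the treatment, research-team raters remain unblinded, and the self-rated Patient Scale is unaffected. The report should state these limits.

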### Secondary outcomes

#### Clinical outcomes

Time to wound healing of study area(s): this is defined as the number of days between burn injury and re-epithelialisation of >95% of the wound surface. Progression of re-epithelialisation is assessed by an experienced burn specialist and reported after every wound inspection.

Wound infection of study area(s): the attending physician will document whether a wound infection has occurred, based on inflammation characteristics (rubor, dolor, calor, tumor, functio laesa) in combination with a positive wound culture.

As of 2009, patient and clinical characteristics are prospectively registered in the Dutch Burn Repository (DBR) R3 in the three Dutch burn centres. Clinical outcomes that will be obtained from DBR R3 are mortality (during admission), time to first excision and grafting, length of hospital stay, length of ICU stay, readmission, reoperation, blood transfusion requirements, wound complications (e.g. graft failure), sepsis, shock, reconstructive surgery, number and timing of outpatient visits. To assess the amount of clinical topical wound treatments, the length of hospital stay will be used as a proxy.

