## Introduction

Burns are one of the most common types of trauma worldwide, causing significant disability [1, 2]. Today, acute burn care in high- and middle-income countries has improved to the point where the focus has shifted from survival as main outcome to outcomes like quality of life, leaving room to broaden our view to other challenges [3]. One of these challenges is the timing of surgery. The severity of a burn, determined primarily by total body surface area (TBSA) and depth of the injury, influences reparative healing potential, and is a primary indicator of the need for surgery [4–6]. For deep partial-thickness burns, currently no consensus regarding the optimal treatment has been reached, which remains a topic of debate [7]. Contrary to superficial partial-thickness burns and full-thickness burns, where the optimal treatment is evident. Superficial partial-thickness burns affect the epidermal and upper dermal layers of the skin, heal within 14 days and do not require surgery [8]. Full-thickness burns fully penetrate all layers of the skin into the subcutis. No spontaneous healing is expected and excision and grafting are always indicated [8–11].

The healing potential of deep partial-thickness burns varies with the longer time to healing being associated with increased scar risk. Two main treatment strategies are currently applied in high- and middle-income countries: 1) conservative treatment with delayed excision and grafting if needed; 2) early excision and grafting. Conservative treatment involves applying dressings and topical antimicrobial and antiseptic agents to the burn, after which spontaneous healing is awaited. If the remaining defects do not heal spontaneously within 14 to 21 days, the burn specialist can decide to perform excision and grafting. In case of early surgery, excision and grafting of the burn is performed within the first week to ten days post-burn [9].

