#### Criteria

Adult (≥18 years) patients with acute thermal burns who are admitted for at least 24 hours or scheduled for surgery are eligible for this study, when the criteria listed below are met.

Inclusion criteria:

Burns with a size of >2.5 centimetres diameter;LDI scan indicating:
Deep partial-thickness burn: yellow wound area on LDI with healing potential between 14 and 21 days, or;Mixed superficial and deep partial-thickness burn: mixed red and yellow wound area on LDI, with a demarcated predominantly yellow area of at least 25cm^2^, or;Mixed full-thickness and deep partial-thickness burn: mixed blue and yellow wound area on LDI, with a demarcated predominantly yellow area of at least 25cm^2^.

The colour codes representing the perfusion units (PU) and healing potential are as follows [8, 23]:

Red/pink: PU 441–2500, healing potential within 14 days;Yellow/green: PU 201–440, healing potential about 14 to 21 days;Blue: PU 0–200, healing potential more than 21 days.

Exclusion criteria:

Frostbite injury [24];Burns suitable for primary closure;Patients unable to complete the Patient and Observer Scar Assessment Scale (POSAS) due to language restrictions or legal incompetence.

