#### Patient and treatment characteristics

Demographics, burn characteristics, and treatment characteristics will be obtained from DBR R3.

Demographics: age, gender, medical history, referral, burn centre. Burn characteristics: TBSA, date of burn injury, burn localisation, burn aetiology, inhalation injury. Treatment characteristics: date of initial surgical intervention and thereby time till first surgical intervention (in days), admission on Intensive Care Unit (ICU), ventilation, topical wound treatments, and wound debridement method, type of grafting, other surgical interventions if applicable.

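### Per-patient secondary outcomes are compared by treatment received, but full-thickness extent, which can affect both group and outcome, is not among the burn characteristics listed

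*Protocol article*

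**What the plan says.** Eligibility is set by wound area. Under Criteria, a burn with full-thickness parts qualifies if it shows "mixed blue and yellow wound area on LDI, with a demarcated predominantly yellow area of at least 25cm^2". The exclusions are frostbite, "Burns suitable for primary closure" and inability to complete the POSAS. None of them limits TBSA or full-thickness extent. Under Burn wound area selection, "A maximum of two inclusion criteria-meeting burns per patient are followed for the study".

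The outcomes sit at two levels. Under Primary outcome and Clinical outcomes, the Observer POSAS, time to healing and wound infection are tied to the study area(s). The registry outcomes are not: the list includes "length of hospital stay, length of ICU stay, readmission, reoperation, blood transfusion requirements", as well as mortality, sepsis and shock. The general scales under Patient reported outcomes (quality of life, physical function, return to work and others) also describe the whole patient, and the questionnaire's own POSAS item concerns a scar that the patient picks.

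Study design assigns patients to a group by the treatment they received; nothing is randomised. Statistical analysis compares the primary and the other outcomes with simple two-group tests, then plans regression to correct for patient, burn and centre characteristics. The burn data to be drawn from the registry appear under Patient and treatment characteristics: "Burn characteristics: TBSA, date of burn injury, burn localisation, burn aetiology, inhalation injury".

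On full-thickness burns the Introduction states: "No spontaneous healing is expected and excision and grafting are always indicated". It also says that severity, determined mainly by TBSA and depth, is a primary indicator of the need for surgery.

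**The concern.** The strategy under study concerns deep partial-thickness burn. Hospital stay, ICU stay, transfusion and reoperation depend on every burn the patient has. In a patient with extensive full-thickness injury, that injury brings its own operations and its own recovery, whichever strategy is used for the deep partial-thickness area.

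If full-thickness extent were balanced between the groups, this would add noise and make a true effect harder to see. The groups are formed by treatment received, however, and full-thickness burn is itself a reason to operate. An imbalance is therefore plausible, and it would enter the comparison as confounding. Total TBSA cannot fully stand in for it, because the same TBSA can be mostly superficial or mostly full-thickness.

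The stakes go beyond the secondary tables. Hospital stay also serves as the proxy for the amount of topical wound treatment, and the Discussion says the results will feed a cost-effectiveness study and a decision aid.

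**Working it through.** The article states no figure on this point that could be reproduced. The check is mainly one of setting its statements side by side.

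**1. Does full-thickness extent affect the outcome?** Yes, on the article's own account. Full-thickness burn always leads to excision and grafting (Introduction), so it contributes to stay, transfusion and reoperation under either strategy.

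**2. Can it affect the group?** Yes. Early surgery is allowed in the first period where judged more suitable for a patient, conservative care is allowed in the second, and the treatment received decides the group (Study design). In addition, the surgical timing items listed (time to first excision and grafting under Clinical outcomes, date of initial surgery under Patient and treatment characteristics) are not tied to the study area. An early operation for a full-thickness area could therefore mark the whole patient as operated early.

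**3. Is it among the listed adjustment data?** No. The burn list holds TBSA, date, localisation, aetiology and inhalation injury. Neither depth nor the study area's share of the burn appears.

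**4. What does adjustment for TBSA leave behind?** Assume a linear model for an outcome such as stay:

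- stay = strategy effect + a × TBSA + b × FT + error, where FT is % TBSA full-thickness.
- If FT is left out, the estimated strategy effect is shifted by b × δ, where δ is the difference in mean FT (early minus conservative) between patients of equal TBSA.

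The article gives neither b nor δ. With b = 1 day per 1% full-thickness, purely as an assumption:

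- FT 4% early v 1% conservative: 1 × (4 − 1) = +3 days
- FT 1% v 1%: 1 × 0 = 0 days
- FT 1% early v 4% conservative: 1 × (1 − 4) = −3 days

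Both size and sign follow from what is assumed. The illustration shows only that TBSA adjustment does not remove the shift.

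**5. How small may a followed area be?** The floor for a mixed burn is 25 cm². Body surface is not given in the article; 1.8 m² (18,000 cm²) is assumed.

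- 25 / 18,000 = 0.139% of body surface
- Range: 25 / 15,000 = 0.167% (1.5 m²) to 25 / 22,000 = 0.114% (2.2 m²)
- Two areas at the floor: 50 / 18,000 = 0.28%
- As a share of the burn at 1.8 m²: 0.139 / 10 = 1.4% at 10% TBSA; 0.139 / 40 = 0.35% at 40% TBSA

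These are eligibility minima for a followed area. They show that the criteria allow other burns to make up nearly all of the injury, not that this is typical.

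**6. Which population was expected?** Under Sample size, the expected maximum of 204 was counted without patients who had full-thickness injuries, whereas Criteria admit mixed full-thickness burns. The count may have dropped only purely full-thickness patients. Either way, it gives no distribution of full-thickness extent among those enrolled.

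**The case against.** A reader might infer that the strategy touches only about 0.14% of body surface, so that the per-patient results simply reflect the other burns. The article does not support this. The 25 cm² is a threshold for a followed area, and the limit of two burns concerns follow-up, not treatment. The strategy can apply to all of a patient's deep partial-thickness burn. Without a distribution of full-thickness extent, nothing can be said about the typical patient.

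A reader might also infer a bias against early surgery, or a difference of a few days in stay. That yellow areas are excised in the same session as full-thickness burns is plausible but stated nowhere, and group membership should depend largely on calendar period, which weakens the link with full-thickness extent. Neither direction nor size can be claimed.

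The strongest objection is that the article plans adjustment for burn characteristics without fixing a closed covariate list, and that the exact model is commonly left to an analysis plan not shown here. This stands as far as the model is concerned. It does not dispose of the point, because the article does set out which burn data will be drawn from the registry, and that list omits a determinant of severity and surgery that its own Introduction names. An analyst working from the listed items could not adjust for it.

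Two further limits stand. The outcomes concerned are secondary. And LDI is done on the physician's indication, so depth may not be mapped for every burn of every patient.

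**Conclusion.** The point holds as a risk of residual confounding in the per-patient secondary outcomes. Four features combine: no limit on full-thickness extent in mixed burns, obligatory surgery for full-thickness burn, groups formed by treatment received, and a list of burn characteristics with total TBSA but no depth. The conclusion assumes that analysts use the listed characteristics and that some enrolled patients have substantial full-thickness burn, which the criteria permit.

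Neither the size nor the direction can be derived from the article; the shift is b × δ with both factors unknown. The Observer POSAS, time to healing and wound infection are measured on the study area, so the concern does not carry over to them in the same way. The change is worth making because it is cheap and the per-patient results have uses beyond this study.

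**What to change.** - Add % TBSA full-thickness to the burn characteristics, taken from existing burn records and LDI scans.
- In the adjusted models for per-patient outcomes (stay, ICU stay, readmission, reoperation, transfusion, general patient-reported scales), enter it as a covariate separate from total TBSA.
- Keep the full cohort as the main analysis. Add a sensitivity analysis limited to patients whose non-superficial burn is mainly deep partial-thickness, with the cut-off fixed before the data are examined. Making this subset the main analysis would cost too much in a cohort of at most 204 and would narrow the real-world scope that the authors chose.
- Report full-thickness extent by group, so that readers can judge the imbalance.

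The cost is modest data extraction. Some values will be missing where depth was not mapped for all burns; their number should be reported and their handling stated. No treatment, visit or eligibility rule changes.
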